Use of any intramuscular uterotonic drug before the birth of the infant is regarded as dangerous because it is not possible to adjust the dosage if it causes hyper-stimulation and cannot be adapted to the level of uterine activity, as is possible with the monitored administration of intravenous oxytocin in health facilities.[11] Hyper-stimulation of the uterus can lead to uterine rupture, fetal asphyxia or fetal demise.[12] [13] These consequences are the basis for the third concern, use of oxytocin prior to delivery of the baby. A recent literature review shows the unsupervised use of uterotonic drugs at home births in South Asia is commonplace, but this has rarely been documented in sub-Saharan Africa [14]. An informal poll of Ghanaian members of the Technical Advisory Group for this study, staff at the Ghana Health Service and health care providers working in Ghana reported that such use was unknown in Ghana. Too few data were identified in the literature review regarding use of uterotonics for labor induction or augmentation at peripheral facilities in sub-Saharan Africa to reach a conclusion. Thus, although the introduction of pharmaceutical uterotonic use at the home could potentially lead to inappropriate use, in Ghana the evidence that is available suggests that this behavior is not already well established. Hence, concerns regarding the safety of providing increased access to pharmaceutical uterotonic drugs are diminished as this is a setting where inappropriate use appears to be unknown. By selecting a uterotonic-naïve setting, one has greater ability to introduce safe home-use of oxytocin via the education components of the intervention. Lastly, results from this proposed study are likely to be generalizable as these characteristics are common across many sub-Saharan African countries.

There are some unpublished studies, as well as anecdotal information from midwives in Ghana, that women turn to traditional preparations (herbs, roots, etc.) to hasten labor. It is not known whether these traditional preparations actually contain uterotonic/pharmacological properties. Biochemical assessment of traditional preparations used at birth is difficult as the chemical qualities of the plants used will vary with rainfall and other environmental conditions and dosage is far from standardized. No literature was identified which suggested possible interactions between oxytocin and such traditional preparations.

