2. ***Study participants*** will consist of pregnant women delivering at home in the presence of a family member and/or traditional birth attendant AND a CHO in demographic surveillance (DSS) areas of the following districts: Kintampo North and South and Nkoranza North and South. District maps are included in Appendices A and B. The Kintampo Health Research Center (KHRC) is one of the three well established field research sites of the Ghana Health Service and has been functioning since 1994. In these districts females constituted approximately 50% of the population with males making up 49%, which is consistent with the national average. Kintampo North and South and Nkoranza North and South districts are predominantly rural with approximately 20% the population residing in urban areas. Subsistence farming is the main activity as most members of the population are uneducated. Less than 10% of the women have completed any training basic training. Ninety-two percent of births to women in these districts received at least one antenatal care visit (and nationally, 77% of births to women received four or more antenatal care visits). Tetanus toxoid immunization coverage in these districts is at 83 percent as of 2009.
3. **Inclusion/exclusion criteria:** Inclusion criteria include: For initial enrollment, all pregnant women at or around seven months gestation who consent to participate in the study should they deliver at home. To reaffirm consent and for final enrollment, all pregnant women who deliver at home in the presence of a CHO and who reaffirm consent to participate in the study. Pregnant women at the time of delivery will be considered emancipated adults, regardless of age. There are no specific exclusion criteria. The percent of women who request CHO presence at birth but for whom a blood loss measurement is not possible due to the late arrival of the CHO, for example, will be reported among the indicators of the feasibility of this intervention.

**Original sample size:**The original sample size for this study was 1,128 pregnant women at the time of birth; Table 1 and the text below summarize those sample size and power calculations. With this amendment of 3/2012, the sample size has been re-estimated. The details and rationale for re-estimating sample size is discussed below under the sub-heading: Re-estimated Sample Size.

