This study was originally designed as a cluster-randomized, community-based trial, conditionally followed by a three month post-comparative universal distribution phase if the intervention is shown to be effective and if members of the Data Safety and Monitoring Board deem this to be appropriate. At the suggestion of the DSMB following the Interim Analysis on 12/15/2012, the conditional Universal Distribution Phase has been eliminated from the protocol (see Section 4 below), as the resources allocated for that Phase must be used to accumulate a larger sample size to improve power to detect any true differences in PPH between the groups. All home-based births attended by a CHO will constitute a cluster for the purpose of this trial. CHOs will be randomized into one of two study arms which will determine the treatment that CHO-assisted home births receive. Fifty-four CHOs will be randomly selected into the intervention or control groups using a computerized selection procedure assuming equal numbers in both groups. Given that the interventions in the two study arms are visible to all present, blinding is not an option for this study. Although the CHOs have approximate catchment areas for which they are responsible, all home births attended by a CHO are potentially eligible for the study, regardless of the geographic location of the birth. The treatment within each arm is described below:

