1. Prevention and early treatment arm: One injection of 10 IU of oxytocin administered via Uniject™ within one minute after delivery of the baby (after first asking the woman if she is pregnant with twins which will be done shortly after arrival at the household and after ascertaining via abdominal palpation that there is no second baby. Abdominal palapation will be done for 100% of women prior to receiving oxytocin injection for prevention or treatment of postpartum hemorrhage). If the woman is actively bleeding (i.e. is experiencing a steady flow) when she has lost 400 mls of blood, referral must be initiated via phone call for emergency transport. To identify active bleeding, the CHO will monitor pulse, uterine tone and vaginal bleeding every 15 minutes for the first two hours. It will be verified that all CHOs have cell phones and units will be provided to them for their participation in this study. KHRC will have a vehicle and driver specifically available for this purpose who will immediately respond to the call. In the event of postpartum hemorrhage (defined as 500mls blood loss), early treatment with one additional injection of 10 IU of oxytocin and fundal massage will be provided by the CHO. In the event of gushing blood, uterus is neither hard nor round and/or clots the size of a lime, following delivery of the baby, CHOs will be trained to administer one injection of 10 IU of oxytocin and fundal massage and will initiate emergency referral, without waiting to verify that 500ml blood loss has been reached. Palpation for a second twin will be done prior to all injections of oxytocin. Emergency referral and transport will be available to women and newborns in both arms of the study for any type of complication. CHOs will be trained to recognize the cause for such referrals before the beginning of the study. CHOs may initiate emergency referral and transport at any time during the intrapartum and immediate postpartum periods per their judgment, based on the training they will receive as part of the Oxytocin Initiative. In the event of an emergency transfer, CHOs will accompany the woman to the hospital and remain there until the woman is admitted to the hospital. For each case of referral, supervisors will verify that referral procedures were followed and documented and any deviations from the protocol will be discussed with the CHO during weekly meetings with the supervisor. Seven days after admission, the CHO supervisor will be responsible for following up with hospital staff in order to document outcomes following the woman or newborn’s discharge from the hospital.

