*Follow up interviews with recently delivered women:* Within 48-72 hours of delivery, the field worker will visit the homes of all women who gave initial consent to participate in the study. The questionnaire will be addressed first to the recently delivered woman enrolled in the study. However, completion of this interview, particularly for questions regarding the timing of administration of the oxytocin or other events during birth, may require input from a family member who was present at the delivery. The purpose of this follow up interview is to a) provide an assessment independent of the CHO regarding the timing of the administration of a uterotonic drug; and b) to document maternal and newborn outcomes which have occurred since the CHO left the household. In the event of an emergency referral at the time of birth, Field Supervisors will be responsible for visiting the hospital to collect information regarding the cause of the referral and the outcomes for woman and baby. At the initial consent, women will have agreed to have this information retrieved from the hospital in the event of an emergency referral. In the event of a maternal death, a family member present at the time of death will be asked consent to be interviewed. A Follow up questionnaire adapted for this purpose has been uploaded as part of this application. In the event of a maternal, fetal or early neonatal death, the internationally accepted WHO verbal autopsy questionnaires for women and infants will be used as an add-on to the Follow Up questionnaire.

*Follow up questionnaire for the non-family member, lay birth attendant:* Within 48-72 hours of delivery, the field worker will visit the non-family member birth attendant who was present at birth to administer a short questionnaire. The purpose of this interview is the same as for the follow up interview with recently delivered women. A consent form for the Follow Up interview specific to the traditional birth attendant is included in this application.

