  2. Safety: adverse maternal and fetal outcomes, including maternal deaths, stillbirths, early neonatal deaths, birth asphyxia; need for newborn resuscitation, uterine rupture; referral and/or transport to a higher-level facility. Comparisons will be made for all deliveries across both arms of the trial and restricted to deliveries for which oxytocin was given before delivery of the baby.
  3. Feasibility: The % of deliveries for which the CHO does not arrive at the pregnant woman’s house in time to intervene. The % of deliveries which occur after dark for which the CHO does not arrive in time to intervene. The average number of minutes required between the call to the CHO and the CHOs arrival at the woman’s house. The % of women who gave initial consent to participate in the study but who does not request CHO assistance at birth. The % of oxytocin in UnijectTM devices that become unusable (according to the time/temperature monitor) over time when stored unrefrigerated, but in a cool place in the CHOs home. The % of oxytocin in UnijectTM devices that are disposed of appropriately. The % of oxytocin in UnijectTM devices distributed to CHOs that cannot be accounted for based on reported use. The reliability of CHO reporting of their own behaviors (the % of deliveries that show discrepancies between practices reported by the CHOs and by the woman/family member one week following delivery).

1. **Human biospecimen collection:**

Postpartum blood will be collected and measured using a calibrated drape designed for this purpose. Used drapes and blood will be disposed of in latrines or in other areas suggested by the family.

1. **Eligibility screening:**

Any woman at or around seven months gestation who agrees to participate in the study should she deliver at home is eligible to be enrolled in the study. Field workers will be responsible for assessing eligibility.

1. **Blinding:**

Given that the intervention CHOs will be administering prophylactic oxytocin in UnijectTM following delivery of the baby, that control CHOs will not be administering prophylactic oxytocin, and that these differences will be visible to all present, blinding is not an option for this study.

1. **Routine care:**

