CHOs in both arms of this trial will not manage deliveries of the women enrolled in the study. Women delivering in the presence of control CHOs will receive the same standard of care they would have received had they not participated in the study, with the important exception that emergency referral and transport can be assured if needed. Women delivering in the presence of the intervention CHOs will receive prophylactic administration of oxytocin in UnijectTM during the third stage of labor, be assured of emergency referral and transport in the event of need, and will otherwise receive the same standard of care they would have received had they not participated in the study.

1. **Placebo or non-treatment:**

A placebo will not be used in this study.

1. **Treatment failure and participant removal criteria:**

Treatment failure is defined as an incident of postpartum hemorrhage following appropriately administered oxytocin in UnijectTM. Participant removal from the study would result from any change in eligibility. Such a change would most likely result from the need for referral to a higher level of medical care prior to administration of the intervention.

1. **Participant therapy at the end of the study:**

When the target sample size has been reached, CHOs will no longer be present for deliveries to administer oxytocin in UnijectTM, unless there are policy changes between now that would permit continued use of oxytocin by CHOs during the third stage of labor. If the results of the study demonstrate both community-level effectiveness in reducing rates of post-partum hemorrhage and an implementation profile that is favorable from safety and logistical viewpoints, the investigators will work closely with local and regional stakeholders to promote change in policy that will facilitate scaling up of the intervention.

1. **Participant referral:**

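### Limiting participants and clusters to home births leaves a woman given oxytocin before birth and then transferred outside the between-arm safety comparison

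*Protocol*

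**What the plan says.** Under Participants, the study population is "pregnant women delivering at home in the presence of a family member and/or traditional birth attendant AND a CHO". Final enrolment, under Inclusion/exclusion criteria, is for "all pregnant women who deliver at home in the presence of a CHO and who reaffirm consent to participate in the study". General study design and methods adds: "All home-based births attended by a CHO will constitute a cluster for the purpose of this trial".

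Secondary objectives 1 and 2 concern oxytocin given before the baby is born, and the maternal and newborn harms associated with its use. The Data analysis plan expresses the first as a percentage of deliveries by arm. For the second it says: "Comparisons will be made for all deliveries across both arms of the trial and restricted to deliveries for which oxytocin was given before delivery". The outcomes listed there include uterine rupture, stillbirth, early neonatal death, asphyxia, and referral or transport to a higher-level facility.

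Three other statements bear on the point:

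- Background and rationale, on oxytocin before birth: "Hyper-stimulation of the uterus can lead to uterine rupture, fetal asphyxia or fetal demise".
- Prevention and early treatment arm: "CHOs may initiate emergency referral and transport at any time during the intrapartum and immediate postpartum periods per their judgment".
- Treatment failure and participant removal criteria: "Participant removal from the study would result from any change in eligibility". The expected cause is a referral that precedes the intervention.

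**The concern.** For the blood-loss outcome the home-birth condition is sensible, because the calibrated drape is used at home. For the safety outcomes the same condition selects women on an event that follows randomisation and that the exposure under study can influence. An injection in labour may cause a complication, the complication may lead to referral, and the birth may then take place in a facility. The woman then fails the enrolment criterion because of what happened after the dose.

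Rationale for the design calls safety as important as the health benefit. Participant therapy at the end of the study makes the promotion of scale-up depend on a favourable safety profile. A frequency of mistimed use computed only among women who stayed home to deliver could look better than the service really is. The condition also fits poorly with the intention-to-treat principle in the Data analysis plan.

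**Working it through.** **Following one woman through the text.** She reaffirms consent when the CHO or field worker arrives in labour (CHO assistance at birth). She is injected before the birth, referred, and delivers in hospital.

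1. Final enrolment requires delivery at home. She does not meet it.
2. A cluster consists of home births. She is in none, although her CHO was randomised.
3. A change in eligibility leads to removal. The example given is referral before the intervention. The intervention is defined as an injection after birth, so her transfer arguably precedes it even though she has had study drug.
4. The safety outcomes are counted per delivery and compared between arms. Nothing there adds births outside the home.
5. Referral or transport is itself a listed safety outcome. Under points 1 and 2 only referrals after a home birth can be counted, so a transfer in labour that ends in a facility birth is lost from its own outcome.

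**Size.** The protocol gives no figure for this comparison, so there is none to reproduce. In one arm, let r be the true share of attended labours with early oxytocin, f the share of those women transferred before birth, and g the share of all other women transferred before birth. All three are assumptions. Among home births the reported rate is

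r(1 − f) / [r(1 − f) + (1 − r)(1 − g)] = r(1 − f) / [1 − rf − (1 − r)g].

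For r = 2%, f = 30%, g = 10%: 0.014 / (1 − 0.006 − 0.098) = 0.014 / 0.896 = 1.56%.

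| True r | f | Reported, g = 0 | Reported, g = 10% |
|---|---|---|---|
| 1% | 10% | 0.90% | 1.00% |
| 1% | 30% | 0.70% | 0.78% |
| 1% | 50% | 0.50% | 0.56% |
| 2% | 10% | 1.80% | 2.00% |
| 2% | 30% | 1.41% | 1.56% |
| 2% | 50% | 1.01% | 1.12% |
| 5% | 10% | 4.52% | 5.00% |
| 5% | 30% | 3.55% | 3.93% |
| 5% | 50% | 2.56% | 2.84% |

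When g = f the reported rate equals r and there is no bias. When g exceeds f the bias reverses: r = 2%, f = 10%, g = 30% gives 0.018 / 0.704 = 2.56%. The direction therefore depends on f being larger than g.

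**Counts.** Re-estimated sample size projects about 1,679 women and reports an intervention-to-control ratio of 0.69 in October 2011. If that ratio holds, the intervention arm has 1,679 × 0.69/1.69 = 686 births. These are enrolled home births, already selected, so the calculation runs backwards from them. Women missing = seen × f/(1 − f), whatever g is.

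- If 1% of the 686 show early oxytocin, 6.9 are seen. With f = 10%, 25% or 50%, the full count is 7.6, 9.1 or 13.7, and with g = 0 the true rate is 1.11%, 1.33% or 1.98%.
- If 2% do, 13.7 are seen. The full count is 15.2, 18.3 or 27.4, and with g = 0 the true rate is 2.22%, 2.65% or 3.92%.

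The effect on harm rates depends further on whether transferred women fare differently from those who stay, for which the protocol has no figure. Control CHOs also carry Uniject devices, so the bias in the between-arm difference depends on r, f and g in both arms.

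**The case against.** The strongest reply is that the safety items do not repeat the word home. They speak of deliveries, and of all deliveries in both arms. The same list contains a feasibility outcome on women who gave initial consent but never asked for a CHO. Those women cannot meet the final-enrolment rule, so not every denominator in the list follows it. This stands as far as it shows that a wider reading is possible. However, that feasibility item names its own denominator and the safety items do not. The only definitions of whose deliveries belong to the trial are the enrolment and cluster definitions.

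A reader might infer that these women go unrecorded. The documents do not support that. The CHO questionnaire covers care from the onset of labour and emergency referral. All women with initial consent are visited at 48-72 hours. For hospital outcomes: "In the event of an emergency referral at the time of birth, Field Supervisors will be responsible for visiting the hospital". Early oxytocin, uterine rupture, stillbirth and maternal death are reportable adverse events with no home-birth limit, and the stopping guidelines consider the timing of oxytocin. The gap lies in the between-arm comparison, since event reports alone do not supply rates on a defined denominator.

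It can also be said that safety sets are commonly left to the SAP. That is fair for missing detail, but here the protocol itself fixes membership through enrolment, cluster and removal rules, and an SAP that follows them inherits the restriction.

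Finally, the rates are assumed, and background transfer can shrink or reverse the bias. That is correct. The protocol also reports that early use appears to be unknown in this setting, so the numbers may be small.

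**Conclusion.** The concern holds in a limited form. Followed as written, the enrolment, cluster and removal rules place a woman dosed early and transferred before birth outside the between-arm safety comparison, by selecting on a post-randomisation event that the exposure can affect. Mistimed use and its harms could then be understated, provided early-dosed women are transferred before birth more often than others. The size cannot be computed from the protocol. With g = 10% and f between 10% and 50%, a true 2% would be reported as anything from 2.00% down to 1.12%.

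A reader might go further and conclude that the most serious mistimed doses are removed, that uterine rupture could hardly be observed, or that harms are understated by more than these ratios. The documents do not support any of these. They say early oxytocin can cause these harms, not that transfer precedes birth in the worst cases, and a rupture may be recognised after a home birth.

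This should be corrected: absolute numbers are probably small, but safety carries weight in the scale-up decision and the correction is cheap.

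**What to change.** Keep the home-birth restriction for the drape-based blood-loss outcome. For secondary objectives 1 and 2, state that the safety population is every woman who reaffirmed consent and whose labour a study CHO attended, or who received any study oxytocin. Analyse her in that CHO's cluster and randomised arm, wherever the birth took place. Count transfers in labour under the referral outcome.

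Reconcile Participants and Inclusion/exclusion criteria, the cluster definition, the Data analysis plan and the removal criteria with this population, so that removal does not take a woman out of the safety analysis.

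The data are already planned: the CHO questionnaire, hospital follow-up after referral, and the 48-72 hour interview. The cost is one definition and a modest amount of analysis. The small downside is that the safety and blood-loss analyses will have slightly different denominators, which the report should show side by side.
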